## Abstract

Attention-deficit/hyperactivity disorder (ADHD) often continues into adulthood and affects several million adults in Germany. Many do not receive timely, evidence-based treatment because of long waiting times and limited access to care. Digital health applications offer a low-threshold option to provide guideline-based support. A pilot study of the present app-based program showed encouraging improvements in quality of life and reductions in ADHD symptom severity.

This randomized controlled trial (RCT) aims to confirm and extend the pilot findings. The primary objective is to examine whether the digital intervention improves quality of life in adults with ADHD. Further outcomes include changes in ADHD symptoms, functional impairment, depressive and anxiety symptoms, substance use, general health, health literacy, medication adherence, and user satisfaction.

A total of 380 adults with verified ADHD will be recruited online and via a university hospital. After informed consent and baseline assessment, participants will be randomized 1:1 to immediate access to a 12-week digital unguided program or to care as usual (CAU). Self-report assessments will take place at baseline, 6 weeks, and 12 weeks. Mixed models for repeated measures will be used for the primary analyses, complemented by intention-to-treat and complete-case approaches.

The trial will test the robustness of the previous pilot results and provide evidence on the clinical value of a scalable digital intervention for adult ADHD.

## Specifications table

**Table utbl0001:** 

**Subject area**	Psychology
**More specific subject area**	*Clinical psychology; digital mental health; adult ADHD treatment*
**Name of your protocol**	*Protocol for a Randomized Controlled Trial Evaluating a Digital Self-Help Intervention for Adults With ADHD*
**Reagents/tools**	*Not applicable. The protocol uses a digital health application (ORIKO^Ⓡ^) and online questionnaires administered via Qualtrics^Ⓡ^. No laboratory reagents or physical equipment are required.*
**Experimental design**	Two-arm parallel randomized controlled trial evaluating a 12-week digital unguided intervention versus care as usual in adults with ADHD, with three assessment time points.
**Trial registration**	*DRKS00037711*
**Ethics**	*The study received approval from the Local Psychological Ethics Committee (LPEK; reference number LPEK-0955) and was conducted in accordance with the ethical standards of the Declaration of Helsinki. Study reporting will adhere to the CONSORT recommendations. While individuals with ADHD contributed to the development of the app, they were not involved in shaping the study design. All participants will give written informed consent prior to enrollment. The trial is prospectively registered in the German Clinical Trials Register (DRKS00037711), where the statistical analysis plan is publicly accessible (*https://www.drks.de/search/de/trial/DRKS00037711*).*
**Value of the Protocol**	• *Aims to confirm and extend findings from a prior pilot study of a digital ADHD intervention* • *Evaluation of effects on quality of life, ADHD symptoms, and broader mental health outcomes* • *Large randomized controlled trial assessing the efficacy of scalable, low-threshold access to care for adults with ADHD*

## Background

Attention-deficit/hyperactivity disorder (ADHD) affects an estimated 1.8–4.7 million individuals in Germany [1]. Around 60 % of those diagnosed continue to experience symptoms into adulthood [2]. Adult ADHD is associated with high rates of psychological and somatic comorbidities, increased health risks, functional impairments, and reduced quality of life [2,3].

Despite its burden, only 10–20 % of affected individuals are correctly diagnosed and treated [3,4]. Among those who receive treatment, the proportion accessing evidence-based care remains low: roughly 30 % receive pharmacotherapy and fewer than 3 % access psychotherapy [2,3]. Barriers include misdiagnosis, limited availability or accessibility, and long waiting times for psychotherapy, often between 6 and 24 months [3,5,6].

Clinical guidelines such as those from the German Society for Psychiatry and Psychotherapy, Psychosomatics and Neurology (DGPPN) [5] and the UK’s National Institute for Health and Care Excellence (NICE) [7] emphasize the need for multimodal, evidence-based interventions that combine psychoeducation, skills training, and, where indicated, pharmacotherapy. Yet, implementation of these recommendations remains inconsistent in routine care.

These gaps highlight the need for low-threshold treatment options. Internet-based interventions (IBI) can address this demand by offering guideline-based interventions, including the recommended psychoeducation and skills training, via smartphone apps. Such approaches may expand access to evidence-based care and reduce treatment delays.

The present protocol builds on a previous pilot trial (DRKS00033320), which provided preliminary evidence that the intervention can improve both quality of life and ADHD symptom burden in adults.

## Objectives

The primary objective of this study is to evaluate the medical benefit of an unguided IBI for adults with ADHD. The main outcome is improvement in self-rated quality of life after completion of the 12-week program. Building on pilot study findings, the trial also aims to confirm the robustness of the intervention’s effect on core ADHD symptoms.

The secondary objectives are to explore reductions in functional impairments, depressive and anxiety symptoms, and substance use, as well as to assess changes in general health status, health literacy, medication adherence, and user satisfaction with the intervention.

## Description of protocol

### Overview

As illustrated in Fig. 1, the trial follows a two-arm randomized controlled design with three assessments. Participants are randomly assigned to either the intervention group (IG) or a care as usual group (CAU). Assessments take place at baseline prior to the intervention (T0), at 6 weeks (T1), and at 12 weeks (T2).

**Fig. 1 fig0001:**
[figure not shown]
Study Flow.

The IG receives immediate access to the 12-week app-based self-help program (ORIKO^Ⓡ^) following baseline, while the CAU group gains access after completion of the final follow-up at T2. All data are collected online.

### Inclusion and exclusion criteria

**Table utbl0002:** 

Inclusion criteria	Exclusion criteria

• Minimum age of 18 years • Diagnosis of ADHD according to ICD-10 or DSM-5, documented with date and diagnosing physician/therapist/institution (e.g., medical report) • Access to a smartphone or tablet • Availability for the 12-week study period • Sufficient knowledge of the German language (speaking, reading, and writing) • Current impairment due to ADHD, indicated by an ASRS Screener score ≥ 14 • Stable ADHD medication regimen for at least 4 weeks prior to study start (no change in type or dosage)	• Current diagnosis of a severe psychiatric disorder, including: • Severe unipolar depression (ICD-10: F32.2) • Bipolar disorder (ICD-10: F31) • Schizophrenia, schizotypal, or delusional disorder (ICD-10: F2) • Borderline Personality Disorder (F.60.3) • Ongoing alcohol and/or drug dependence (ICD-10: F1x.2) • Current suicidality (past six months) • Ongoing participation in ADHD-specific psychotherapy • Current initiation or adjustment of ADHD-specific pharmacotherapy (e.g., methylphenidate, amphetamine, atomoxetine)

### Recruitment

Recruitment will be conducted via the University Medical Center Hamburg-Eppendorf (UKE). In addition, further recruitment will take place through other sources including email contact with individuals who previously expressed interest in the pilot study (DRKS00033320), referrals by clinicians at the specialized ADHD outpatient clinic of the UKE, online advertisements (e.g., social media and patient organizations such as *ADHS Deutschland e.V.*), and self-initiated contact by interested individuals via a dedicated study email address. The planned recruitment period is three months. Individuals recruited online must submit written proof of their diagnosis before they can access the baseline survey. Participants may withdraw from the study at any time without providing a reason and without any negative consequences for their medical treatment or relationship with healthcare providers. Participation is voluntary and independent of routine care. Although recruitment occurs partly within healthcare settings, treating clinicians are not involved in obtaining consent, and refusal or withdrawal does not affect access to treatment as usual.

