**Outcomes**					
AAQoL			X	X	X
ASRS			X	X	X
CGI-S			X	X	X
PHQ-9			X	X	X
GAD-7			X	X	X
AUDIT-C/DUDIT			X	X	X
HLS-EU			X	X	X
BFIS			X	X	X
MARS-D			X	X	X
CSQ-8				X	X

Notes: 'Sociodemographics' includes information on gender, age, education, nationality, and native language; 'Care as usual' includes information on previous psychotherapy and current medication with psychotropic drugs (including dosage).

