### Statistical analyses

#### Sample size

The sample size was calculated in G*Power (version 3.1) [26] for an independent-samples *t*-test targeting the primary endpoint. Assuming a medium effect (Cohen’s *d* = 0.40), two-tailed α = 0.05, and 1−β (power) = 0.90, the required total sample is *N* = 266 (133 per group). Because digital interventions commonly face attrition around 25 % (e.g., [27]), we inflated the sample by 30 %. The resulting recruitment target is *N* = 380 (*n* = 190 per group). This calculation is conservative relative to the mixed-models approach planned for the primary analysis. All analyses will be performed using IBM SPSS^Ⓡ^ Statistics 31 and R 4.4.3 [28].

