#### Exploratory analyses

Subgroup analyses will be conducted for primary and secondary outcomes by age (≤65 vs. >65 years), gender (male/female/diverse), current medication status (yes/no), and app use (dichotomized at median module completion). In addition, exploratory analyses will examine changes in perceived self-stigmatization, as measured by the ISMI-9.

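### Recruitment draws on people interested in the pilot of the same app, but no eligibility criterion excludes pilot participants or earlier ORIKO users

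*Protocol article*

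**What the plan says.** Under Recruitment, the protocol article names several sources. One is "email contact with individuals who previously expressed interest in the pilot study (DRKS00033320". Another is "self-initiated contact by interested individuals via a dedicated study email address".

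The Abstract makes clear that the pilot used the same intervention: "A pilot study of the present app-based program showed encouraging improvements in quality of life and reductions in ADHD symptom severity". It also states the purpose of the new trial: "This randomized controlled trial (RCT) aims to confirm and extend the pilot findings".

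The section on inclusion and exclusion criteria gives an itemised two-column list. No item concerns participation in the pilot or previous use of ORIKO. The nearest exclusion is "Ongoing participation in ADHD-specific psychotherapy", which concerns current treatment.

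The schedule of assessments (Table 2) lists sociodemographics, experience with psychotherapy and care as usual among the background items. Its note reads: "Care as usual' includes information on previous psychotherapy and current medication with psychotropic drugs (including dosage". Prior app use is not named. The planned subgroups under Exploratory analyses are age, gender, "current medication status (yes/no), and app use (dichotomized at median module completion". The last of these concerns use during the trial, not before it.

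**The concern.** The trial contrasts immediate with delayed access to a 12-week program. That contrast is cleanest when nobody has already been through the program. An earlier user allocated to the control arm is not waiting for first access, and an earlier user in the intervention arm may have less left to gain. Both would shrink the difference between arms.

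The second matter is the confirmatory aim. To the extent that pilot participants re-enter, the two samples overlap and the new result is less independent of the pilot.

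As the data collection is listed, the trial report might also be unable to say how many participants were exposed, or to show the result without them.

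**Working it through.** **Step 1. Is the route open?** Three sections have to be read together.

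- Recruitment: people who showed interest in the pilot are emailed, and anyone may write in unprompted.
- Abstract: the pilot intervention is the present program.
- Eligibility criteria: nothing bars a person who has already used it. The Intervention section describes the app as a form of digital psychotherapy, so current use might arguably fall under the exclusion of ongoing ADHD-specific psychotherapy. Past use would not.

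A person who completed the program in the pilot and meets the other criteria is therefore eligible as the text stands.

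**Step 2. Reproduce the plan's sample size.** The Sample size section gives the inputs: "Assuming a medium effect (Cohen’s *d* = 0.40), two-tailed α = 0.05, and 1−β (power) = 0.90", for an independent-samples t-test with 1:1 allocation.

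- The noncentral t solution is 132.3, so 133 per group and 266 in total. This matches the plan.
- Power at 133 per group: noncentrality 0.40 × √(133/2) = 3.26 on 264 degrees of freedom, which gives 0.901.
- Inflation for 30% loss: 266 / (1 − 0.30) = 380, or 190 per group. This matches the plan.

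There is no arithmetic error in the plan.

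**Step 3. Illustrate dilution.** Let f be the share of participants already exposed and r the effect in exposed people as a fraction of the effect in unexposed people. Neither is given in the document, so both are assumptions. I also assume that f is the same in both arms, that loss to follow-up does not depend on exposure, and that the standard deviation is unchanged. Then

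d_eff = 0.40 × [(1 − f) + f × r].

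For example, f = 10% and r = 0 gives 0.40 × 0.90 = 0.36; f = 10% and r = 0.5 gives 0.40 × 0.95 = 0.38.

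| Exposed share f | Number among 380 | d_eff, r = 0 | Power, 133/arm | d_eff, r = 0.5 | Power, 133/arm |
|---|---|---|---|---|---|
| 0% | 0 | 0.40 | 0.90 | 0.40 | 0.90 |
| 5% | 19 | 0.38 | 0.87 | 0.39 | 0.89 |
| 10% | 38 | 0.36 | 0.83 | 0.38 | 0.87 |
| 20% | 76 | 0.32 | 0.74 | 0.36 | 0.83 |

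**Step 4. Sensitivity to attrition.** The 133 per arm correspond to 30% loss. The plan expects about 25%, and 190 × 0.75 = 142.5, so about 142 per arm would remain. Power for f = 5, 10 and 20% is then 0.89, 0.86 and 0.77 with r = 0, and 0.91, 0.89 and 0.86 with r = 0.5.

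**The case against.** The strongest reply is that the text never says pilot participants are contacted. Showing interest is not the same as taking part, and the list may consist largely of people who enquired and were never enrolled. The article is also a condensed document, and the mailing could be filtered in a way it does not describe. The first part stands: a reader might infer that exposed people are being re-recruited, and the document does not establish that. The second part carries less weight. Eligibility criteria are not normally left to an analysis plan, the list is given item by item, and filtering the mailing would not stop self-referral.

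A second reply is that the harm is limited and may run either way. This largely stands. Prior exposure is fixed before randomisation and balanced in expectation, so it does not confound the comparison. Pure dilution is conservative. The ASRS Screener threshold of 14 keeps out earlier users who have fallen below it. Conversely, people who liked the app may be the ones who return, which could push the estimate up.

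A third reply is that the power figures rest on invented shares. They do. The document gives neither the size of the pilot nor the length of the interest list, and zero residual benefit is the extreme case. The Sample size section also calls its t-test calculation conservative relative to the mixed model.

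Two further inferences are tempting and not supported. One is that the care-as-usual record is confined to psychotherapy and medication. The Table 2 note says what the record includes, not that it holds nothing else. The other is that control participants could use the app unnoticed during the trial. Access is by a code given to the intervention arm, the control arm receives access only after the 12-week assessment, and log files track use. Concurrent use is in any case a different question from earlier use.

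**Conclusion.** The point holds as a gap in eligibility. A pilot-linked mailing and open self-referral are combined with criteria that do not address earlier use of the same app, and no listed baseline item would identify it. Exposure is permitted, not demonstrated.

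If exposed people do enter, the consequences are an attenuated estimate, reduced power, and weaker independence from the pilot in proportion to the overlap. A reader might go further and say that the trial cannot confirm the pilot, or that its comparison is biased by confounding. The document supports neither.

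The size is unknown. On the assumptions in the table, power falls from 0.90 to between 0.74 and 0.89 for exposed shares of 5 to 20%. If nobody exposed is enrolled, the loss is nil. This does not invalidate the trial, but it is an avoidable weakness in a confirmatory design and is much easier to prevent than to repair afterwards.

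**What to change.** Add to the exclusion criteria: participation in DRKS00033320 or any previous use of ORIKO. Check it with one screening question and against the pilot's ID list.

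If recruitment has begun, record prior exposure for those already enrolled and repeat the primary analysis without them as a sensitivity analysis. Because exposure precedes randomisation, removing exposed people from both arms keeps the comparison randomised. The pilot's ID list is the better source for this, since it does not depend on recall or on who answers the follow-up surveys.

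The cost is a minor amendment, one screening question and the loss of a few easily reached recruits. The sample size of 266 evaluable and 380 recruited is unchanged, because it already assumes the full effect of d = 0.40 throughout the sample.

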### Randomization and blinding

Participants are randomized automatically in a 1:1 ratio (IG vs. CAU) using an algorithm embedded in the online survey platform Qualtrics^Ⓡ^. Randomization occurs after informed consent and completion of the baseline assessment, minimizing allocation bias. Group allocation is disclosed to participants at the end of the baseline survey, as blinding is not feasible: no placebo condition exists, and participants must know whether they receive immediate or delayed access to the app.

Data collection is based entirely on digital self-report questionnaires administered through Qualtrics, eliminating potential assessor bias. Because allocation is automated and outcome scoring is standardized, neither study staff nor data analysis procedures are subject to manipulation.

### Care as usual

The intervention is designed to be delivered within routine healthcare. Participation in the study does not preclude concurrent treatment; therefore, ongoing CAU is permitted. CAU may include, for example, the use of psychotropic medication. Medication use, including type and dosage, will be documented at baseline (T0) and reassessed at both follow-ups (T1 and T2).

### Intervention: ORIKO^Ⓡ^

The ADHD therapy app ORIKO is a digital self-help program developed for adults aged 18 years and older. It is designed to complement standard treatment provided by general practitioners or specialists, with the overarching goal of improving health status in individuals with ADHD. Consistent with guideline recommendations for adults with ADHD [2,3,5,8], the app provides digital psychotherapy based on cognitive-behavioral therapy (CBT), dialectical behavioral therapy (DBT), and social skills training (SST). Psychoeducational modules are also included to enhance knowledge and support self-management. The structured therapy pathway consists of 12 sequential modules developed by clinical experts in ADHD psychotherapy. Content is delivered through short video sequences featuring physicians, psychotherapists, and individuals with ADHD, and is accompanied by exercises that facilitate transfer into everyday life. An overview of the modules can be found in Table 1.

**Table 1 tbl0001:** Overview of intervention modules.

Module Category	Module Title
Introductory	Goal setting, motivation, program overview, general psychoeducation, resource activation
Symptom-focused	Attention and focusing
Symptom-focused	Organization and structure
Symptom-focused	Time perception and management
Symptom-focused	Impulse control
Symptom-focused	Emotional regulation, affective stability
Symptom-focused	Managing motor restlessness
Cross-symptom	Procrastination and avoidance
Cross-symptom	Social interactions and communication
Cross-symptom	Self-care
Cross-symptom	Sleep and recovery
Final	Relapse prevention (long-term maintenance)

Note. Modules are structured into introductory, symptom-focused, cross-symptom, final, and optional categories.

### Procedure and assessments

Potential participants are recruited at UKE or via online outreach and receive detailed study information along with a link to the digital informed consent form and baseline survey (T0). After consent, they complete the questionnaires listed in Table 1. Participants are then randomized (see Randomization and Blinding). Those allocated to the IG receive an access code to the app, while the CAU receives access after the final assessment (T2). Identical surveys are administered at 6 weeks interim (T1) and 12 weeks (T2), with the IG additionally completing the CSQ-8 at T1 and T2. At each assessment, medication status and CAU are recorded. Participants are compensated with an online shopping voucher upon completion of follow-up assessments.

### Measures

An overview of the assessment time points is provided in Table 2.

**Table 2 tbl0002:** Schedule of assessments.

		Baseline (T0)		Interim (T1)	Post (T2)
		Prior to randomization		Week 6	Week 12
		Screening	Assessment		
Informed consent		X			
Sociodemographics*		X			
Self-stigma (ISMI-9)			X	X	X
Experience with psychotherapy		X			
Inclusion/exclusion		X			
Care as usual*			X	X	X
**Outcomes**					
AAQoL			X	X	X
ASRS			X	X	X
CGI-S			X	X	X
PHQ-9			X	X	X
GAD-7			X	X	X
AUDIT-C/DUDIT			X	X	X
HLS-EU			X	X	X
BFIS			X	X	X
MARS-D			X	X	X
CSQ-8				X	X

Notes: 'Sociodemographics' includes information on gender, age, education, nationality, and native language; 'Care as usual' includes information on previous psychotherapy and current medication with psychotropic drugs (including dosage).

### Primary

#### Quality of life

The Adult ADHD Quality of Life Scale (AAQoL) [9] is the primary outcome. This 29-item self-report instrument covers four domains: life productivity, psychological health, life outlook, and relationships, rated on a 5-point Likert scale (1 = not at all/never, 5 = extremely/very often). Internal consistency is rated excellent (Cronbach’s α = 0.93).

### Secondary

#### ADHD symptoms

The Adult ADHD Self-Report Scale (ASRS) [10] includes 18 items scored from 0 (never) to 4 (very often). It yields a total score (0–72) and two subscales: inattention and hyperactivity/impulsivity (0–36 each). Internal consistency is considered good (Cronbach’s α = 0.88).

#### Functional impairment (global)

ADHD-related impairment in daily life is assessed with an adapted item from the Clinical Global Impression – Severity scale (CGI-S) [11]. Participants rate their impairment on a 7-point Likert scale from not at all impaired (1) to severely impaired (7).

